### Recruitment {15}

To optimize patient enrollment, nursing and medical staff will screen all admissions for patients with cirrhosis into the ICU and signal them to the P.I. for timely recruitment.

## Assignment of interventions: allocation

### Sequence generation {16a}

The patient allocation method consists of stratified randomization with blocks within each subgroup. This method is particularly useful with randomizing small samples due to the ability to create balanced groups regarding predetermined variables or characteristics at the beginning of the trial, reducing differences in baseline trial groups characteristics’ that could harm later result analysis and conclusions.

In this small sample size trial, patients will be stratified according to maximum serum creatinine and maximum IAP, expected to be the two most important variables to balance between trial groups at baseline. Stratified randomization will homogenize trial groups ad initio to reduce the probability of unbalanced baseline group characteristics and biased results.

The stratification process will use two strata, namely, maximum IAP and maximum serum creatinine, thus creating four subgroups (I–IV): (I) IAP < 16 mmHg + serum creatinine < 1.5 mg/dL, (II) IAP < 16 mmHg + serum creatinine ≥ 1.5 mg/dL, (III) IAP ≥ 16 mmHg + serum creatinine < 1.5 mg/dL, and (IV) IAP ≥ 16 mmHg + serum creatinine ≥ 1.5 mg/dL [4, 13]. Each subgroup (I–IV) contains sequential blocks of randomized trial group allocation (A) control and (B) intervention, with a 1:1 ratio (i.e., *AABB*, *ABAB*, *BABA*, *BBAA*), as exemplified in Table 1.

**Table 1 Tab1:** Stratification subgroups (I-IV) created using maximum intra-abdominal pressure (IAP) and serum creatinine as strata. Example of stratified randomization with blocks within each subgroup (A, B)

Stratification subgroups (I–IV)	Creatinine < 1.5 mg/dL	Creatinine ≥ 1.5 mg/dL
IAP < 16 mmHg	I) ABAB, ABBA,…	III) BABA, BBAA,…
IAP ≥ 16 mmHg	II) BABA, AABB,…	IV) BBAA, BAAB,…

### Concealment mechanism {16b}

The adopted concealment mechanism of the allocation sequence will use sequentially numbered (#), opaque, sealed envelopes, and the random sequence for trial group allocation in blocks will be generated by the P.I. using an online tool [33].

To prevent biased selection of patients, the PI will remotely screen for new patient admissions and alert the ICU staff for possible candidates. The patient’s attending physicians are responsible for applying protocol, deciding patient eligibility, and checking for inclusion/exclusion criteria and obtaining the informed consent.

Once patient enrollment has been established, the attending physicians, who are blinded for the allocation blocks, will determine the corresponding stratification subgroup by using IAP and creatinine values and open the respective sealed envelope containing the group allocation. The PI will provide any required assistance, and, finally, be informed of the patient allocation.

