### Plans to promote participant retention and complete follow-up {18b}

The P.I. will promote participant retention and complete follow-up by daily checking with the clinical staff for new eligible patients, assuring protocol adherence and complete follow-up during the ICU and hospital stays of enrolled patients.

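### The P.I. both generates the allocation sequence and flags candidates, so P.I. screening cannot be presented as a guard against biased selection

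*Protocol article*

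**What the plan says.** Concealment mechanism {16b} gives the P.I. the sequence: "the random sequence for trial group allocation in blocks will be generated by the P.I. using an online tool". It also gives the P.I. a part in finding patients: "the PI will remotely screen for new patient admissions and alert the ICU staff for possible candidates". The article introduces that second task as a measure against biased selection.

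The ward's own screening leads to the same person. Under Recruitment {15}, "nursing and medical staff will screen all admissions for patients with cirrhosis into the ICU and signal them to the P.I. for timely recruitment". The retention section {18b} adds that the P.I. will be "daily checking with the clinical staff for new eligible patients".

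The enrolment decision itself lies elsewhere: "The patient’s attending physicians are responsible for applying protocol, deciding patient eligibility, and checking for inclusion/exclusion criteria and obtaining the informed consent". Those who choose the stratum and open the envelope are "the attending physicians, who are blinded for the allocation blocks". Then: "The PI will provide any required assistance, and, finally, be informed of the patient allocation".

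The Discussion lists selection bias from fixed blocks as a limitation. Its response is that the attending physician, not the P.I., reveals the allocation.

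**The concern.** Allocation concealment requires that nobody who affects whether or when a patient enters can know the next assignment. Sealed opaque envelopes achieve this for the attending physicians. They do nothing for the person who produced the sequence, and here that person also flags candidates. Calling P.I. screening a protection therefore gets the logic the wrong way round: it places the one person who may know the list at the point where patients are put forward.

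This is separate from physicians guessing the end of a fixed block. Varying the block lengths would help with guessing but not against someone who holds the list.

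What is at stake is baseline comparability in an open-label, single-site trial of 70 patients. The Discussion relies on randomization to balance patients so that creatinine can be compared between groups. Stratifying on one creatinine cut-off and one IAP cut-off would not repair differences in other prognostic features caused by who was flagged, or when.

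**Working it through.** There is no stated figure to reproduce. The check follows each role through the article.

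1. **Generating the sequence:** the P.I. ({16b}).
2. **Identifying candidates:** the P.I. remotely ({16b}), and nursing and medical staff in parallel, who then pass patients to the P.I. ({15}). The P.I. also asks about eligible patients every day ({18b}).
3. **Eligibility, exclusions and consent:** the attending physician ({16b}). When a patient cannot decide and no surrogate is at hand, the P.I. and another ICU professional try to reach a surrogate ({26a}).
4. **Choosing the stratum and opening the next envelope:** the attending physician ({16b}, {16c}).
5. **Learning the result:** the P.I. is told every allocation ({16b}).
6. **Blind to the blocks:** stated for the attending physicians only. No section says it of the P.I.
7. **Preparing and keeping the envelopes, and keeping the list:** not stated.

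Roles 1, 2 and 5 meet in one person. The safeguard in the Discussion acts at role 4 and leaves role 2 untouched.

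For the next allocation to affect flagging, two further conditions are needed, and the article states neither: (a) the P.I. retains the list, and (b) the P.I. knows the patient's stratum when deciding whether to alert. On (b), the strata use maximum IAP and maximum creatinine ({16a}), IAP is measured every 6 to 8 h ({11a}), and the attending physician sets the stratum once enrolment is established.

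As an illustration, suppose (a) is false and the P.I. relies only on the reported allocations and on knowing that blocks have length 4, as in the examples in {16a}. Count the assignments that are certain from the earlier ones in the same block.

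- All six balanced orders in use (all six appear across Table 1): the fourth position is always certain, 6 of 6. The third is certain only after AA or BB, 2 of 6. The first and second never are. Total (6 + 2) / (6 × 4) = 8/24 = 33%.
- Only the four orders listed in the text of {16a}: the first two letters identify the block, so positions three and four are always certain. Total (4 + 4) / (4 × 4) = 8/16 = 50%.

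So discarding the list would reduce what the P.I. can know, but would not remove it. These percentages also assume that the P.I. tracks which stratum each past patient belonged to. They describe predictability and not bias.

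**The case against.** The strongest reply is that the P.I. admits nobody. Attending physicians check every criterion, take consent, set the stratum and open the envelope, and are described as blind to the blocks. The judgement-based exclusions (futility, expected short stay) are in clinical hands. Staff screen every admission for cirrhosis, so a patient the P.I. does not flag can still be found, and no P.I. veto is stated. Allocation must fall within the first 24 h of the stay ({13}), which limits delay. The daily check in {18b} gives no gatekeeping power. Envelope custody is a detail that an article may leave to the full protocol.

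All of this stands, and it makes the route narrow: what remains is selective or delayed alerting. It does not rescue the statement in {16b}, because screening by the author of the list cannot be what prevents biased selection. The parallel staff screen also reports to the P.I., so it is not fully independent.

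A reader might infer that concealment has failed, that every next allocation is known to the P.I., or that the stratum is known before the alert goes out. The documents support none of these. They do not say that the P.I. keeps the list or sees IAP values when screening, and the stratum is formally set after enrolment.

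**Conclusion.** The point holds in limited form. The article describes an arrangement that weakens concealment and misdescribes one part of it as a safeguard. This is stated text and not a detail left out.

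That the next allocation could influence flagging rests on two assumptions: that the P.I. retains (or can partly reconstruct) the list, and that the P.I. knows the patient's stratum in time. The size of any resulting bias cannot be derived from the article. Nothing suggests that selection has in fact occurred, and no misconduct is implied. Sample size, endpoints and clinical procedures are unaffected. It should be corrected, because the remedy is cheap compared with the doubt it removes.

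**What to change.** - Have the remaining sequence generated and held, and the envelopes prepared, by someone with no screening or enrolment role. The statistician on the data monitoring committee ({21a}) or another independent person would do. Start new blocks in each of the four strata, and withhold the list from the P.I. until recruitment ends. The P.I. can then go on screening.
- Amend {16b} so that P.I. screening is no longer described as preventing biased selection, and state who prepares and keeps the envelopes and the list.
- Report how many patients were enrolled under the present arrangement.

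Cost: a short amendment notified to the Research Center and Ethics Committee ({25}), and preparation of new envelopes. Part-used blocks would be closed early. With blocks of four, that leaves an imbalance of at most 2 patients per stratum, so at most 4 × 2 = 8 over the four strata if all fell the same way; partial cancellation is more likely. Patients already enrolled stay under the present arrangement. If recruitment has already finished, the corrected statement and the disclosure are still worth making.

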### Implementation {16c}

The allocation mechanism will be implemented by the patient’s attending physician, after determining the stratification group (I–IV) by opening the corresponding envelope with the lowest available number (#).

## Assignment of interventions: blinding

### Who will be blinded {17a}

Given the open nature of the trial, the assigned interventions will be unblinded for the clinical staff and patient. Outcome assessment and data analysts will also be unblinded for patient’s group allocation given the objective character of the outcomes and the open trial intervention.

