### Relevant concomitant care permitted or prohibited during the trial {11d}

There are no restrictions to patient care during this trial.

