### Outcomes {12}

The primary outcome is serum creatinine concentration. The secondary outcomes are IAP, measured creatinine clearance, daily urine output, the multiorgan disfunction score Chronic Liver Failure Sequential Organ Failure Assessment (CLIF-SOFA) [13] and the incidence of stage 3 acute kidney injury (AKI) (defined by Kidney Disease: Improving Global Outcomes—KDIGO AKI [29] score), as well as 28-day renal replacement therapy (RRT)-free days, 28-day survival rate, and ICU LOS. The outcomes variables will be assessed at day seven (D7) after randomization (D0), unless otherwise stated. Additionally, IAP, serum creatinine concentration, measured creatinine clearance, daily urine output, and CLIF-SOFA will be analyzed using their maximum or minimum and daily mean values between D1 and D7.

Whenever ICU discharge or liver transplant occurs before D7, the last available data prior to these events will be used for outcome assessment. Additionally, stage 3 AKI will be considered when RRT or death occurs and, in these circumstances, a serum creatinine concentration value of 4 mg/dL and creatinine clearance value of 10 mL/min will be used for outcome assessment as mentioned in the literature [13, 29, 30].

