## Statistical methods

### Statistical methods for primary and secondary outcomes {20a}

For the descriptive analysis, quantitative variables will be reported as means and standard deviations or as medians and interquartile ranges (*P*_25_-*P*_75_), as appropriate, and categorical variables reported as frequencies and percentages.

Quantitative variables will be analyzed using the assessment day value (D7), the daily mean value, and their maximum or minimum values. Mann–Whitney *U* test will be used to compare study groups, assuming a non-normal distribution, or two independent sample *t*-test, in case of normal distribution. Dichotomous categorical variables will be analyzed using chi-square or Fisher’s exact tests. Using daily values, mixed effects regression models will be used to consider the autocorrelation structure between the longitudinal measurements. Regarding stage 3 AKI as secondary outcome, odds ratios and corresponding 95% confidence intervals will be estimated using logistic regression models. For the study of RRT-free days, competing risks survival models will be applied considering death as the competing risk. Regarding time until death, joint survival regression models will be used to take into consideration the association of longitudinal markers with time until death. For LOS, linear regression models will be applied. For all regression studies, univariable and multivariable analyses will be performed to account for potential confounders. The absolute risk of paracentesis-related complications will be reported for both trial groups. A level of significance *α*= 0.05 will be considered. Data will be analyzed using the R Statistical Software [41].

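### Unblinded assessment and analysis is justified by objective outcomes, but a start of renal replacement therapy by staff who know the arm sets the primary creatinine to 4 mg/dL

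*Protocol article*

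**What the plan says.** Who will be blinded {17a} states that "the assigned interventions will be unblinded for the clinical staff and patient". It continues: "Outcome assessment and data analysts will also be unblinded for patient’s group allocation given the objective character of the outcomes", and adds the open intervention as a second reason, so that the full clause reads "group allocation given the objective character of the outcomes and the open trial intervention".

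Outcomes {12} states that "The primary outcome is serum creatinine concentration", assessed at day 7 (D7). It then adds a scoring rule: "stage 3 AKI will be considered when RRT or death occurs", and in those circumstances "a serum creatinine concentration value of 4 mg/dL and creatinine clearance value of 10 mL/min will be used for outcome assessment".

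Criteria for discontinuing or modifying allocated interventions {11b} gives the attending physician the final word on clinical decisions. Relevant concomitant care {11d} says: "There are no restrictions to patient care during this trial". Under Implementation {16c}, the attending physician opens the allocation envelope.

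**The concern.** The objectivity argument covers a measured creatinine and it covers death. It does not cover a value assigned because a clinician started a treatment. One RRT start, made with knowledge of the arm, replaces the primary value by 4 mg/dL. The same start sets clearance to 10 mL/min, counts the patient as stage 3 acute kidney injury and reduces RRT-free days.

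If knowledge of the arm led to RRT being started at a lower creatinine in one arm, the primary difference would move without any difference in renal function. The assigned value also lies far from the values assumed in the design, so a few patients carry much weight.

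**Working it through.** **Inputs from the article.** Sample size {14}: target difference 0.4 mg/dL; means 0.9 (SD 0.45) and 1.3 (SD 0.48); one-sided alpha 0.05; 95% power; 60 patients, raised to 70, allocated 1:1, so 35 per arm. Outcomes {12}: assigned value 4 mg/dL.

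**The plan's own figure.** Pooled SD = √((0.45² + 0.48²)/2) = 0.465. A two-sample noncentral t calculation with difference 0.4, one-sided alpha 0.05 and 95% power gives 30 per arm, 60 in total. The stated figure is reproduced. On this scale, 4 mg/dL lies (4 − 1.3)/0.465 = 5.8 SDs above the higher design mean.

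**Shift from excess RRT starts.** Let k be the excess number of starts in one arm and c the creatinine (mg/dL) those patients would otherwise have had. The difference in means moves by k × (4 − c)/35. The documents give neither k nor c, so both are assumptions. For k = 3:

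| c | shift (mg/dL) | share of 0.4 |
|---|---|---|
| 1.3 | 3 × 2.7/35 = 0.23 | 58% |
| 2.0 | 3 × 2.0/35 = 0.17 | 43% |
| 3.0 | 3 × 1.0/35 = 0.09 | 21% |
| near 4 | near 0 | near 0% |

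**Excess needed to produce the whole 0.4 mg/dL with no true effect.** This is 35 × 0.4/(4 − c):
- c = 1.3: 5.2 patients of 35
- c = 2.0: 7 patients of 35
- c = 3.0: 14 patients of 35

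**Effect on the tests.** 10,000 trials were simulated with 35 per arm and the same lognormal creatinine distribution in both arms (mean 1.1, SD 0.465; or mean 2.0, SD 1.0). Values were replaced by 4 at random at assumed rates. The ranges span the two distributions.

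| Assumed rates | Two-sided t-test | Mann–Whitney (two-sided) |
|---|---|---|
| 20% v 20% | about 5% | 4% to 5% |
| 30% v 20% | 10% to 15% | 10% to 11% |
| 40% v 20% | 28% to 42% | 27% to 31% |

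Equal substitution rates do no harm to the error rate. Unequal rates do, and a rank test does not remove the effect.

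**The case against.** The strongest reply is that the route is hypothetical. {11b} and {11d} speak of care in general and do not mention RRT, so discretion over RRT is an inference. The article condenses a longer protocol that may hold criteria for starting it. No RRT rate, imbalance or direction is given. All of this stands, and it limits the point to a reason that does not hold plus a possible bias. It does not rescue the reason, because the scoring rule and the unblinded staff are both in the text.

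Three stronger readings are tempting and are not supported.

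- A reader might infer that an unblinded analyst is free to choose among the D7, mean, maximum and minimum values, because {20a} says "Quantitative variables will be analyzed using the assessment day value (D7), the daily mean value, and their maximum or minimum values". But Outcomes {12} makes D7 the assessment day and calls the other summaries additional. What is tied to the data is the choice between t-test and Mann–Whitney. The covariates are not named, which is a detail commonly left to an analysis plan.
- A reader might infer that no planned analysis bears on the issue. RRT-free days are compared between arms with competing-risks models, and daily urine output carries no assigned value. Together they could reveal an imbalance. They do so only indirectly, and they do not re-estimate the primary outcome.
- A reader might take masking of the analyst to be free of cost, or to be a cure. Ascitic fluid is resampled every 48 hours only in the intervention arm ({11a}, {18a}), so a full dataset reveals the arm unless it is stripped. The RRT decision is made at the bedside, where coded data change nothing.

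The second reason in {17a}, the open intervention, explains why clinicians cannot be masked. It does not by itself prevent an arm-coded analysis file.

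Finally, the last creatinine before RRT may score a very ill patient leniently, which the 4 mg/dL rule avoids. That is a fair reason to keep the rule as primary.

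**Conclusion.** The point holds in a limited form. The objectivity reason in {17a} does not cover the RRT-triggered part of the primary outcome, because that part depends on a treatment decision made with knowledge of the arm. With 35 per arm, 3 excess starts would be worth 21% to 58% of the target difference for an otherwise expected creatinine of 3.0 down to 1.3 mg/dL, and almost nothing near 4. These sizes rest on assumed counts and creatinine values; the documents supply neither.

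A reader might infer that the primary result will be biased, or biased in favour of the intervention. The documents support neither inference: they show only that the route is open and that no stated analysis re-estimates the primary outcome without the assigned RRT value. This is a worthwhile, inexpensive improvement and not a fatal flaw.

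**What to change.** 1. **Outcomes {12} and Statistical methods {20a}.** Keep the 4 mg/dL rule for the primary analysis. Prespecify a supplementary analysis of D7 creatinine that uses, for RRT patients, the last measured value before RRT started, with 4 mg/dL retained for death. Tabulate creatinine and urine output at RRT start by arm, from the daily data already collected.
2. **Who will be blinded {17a}.** Remove the objective character of the outcomes as the reason for unblinded analysis. Give the analyst of the primary outcome a dataset with arms coded X and Y, with arm-revealing variables such as the 48-hourly ascitic samples removed. Unmask only once the choice of t-test or Mann–Whitney and the covariates are locked. State that this protects against analysis choices only and not against the RRT route.

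The cost is preparing one coded and stripped dataset, one table and one extra estimate. That estimate may differ from the primary result and treats RRT patients more leniently, so it should be labelled a supplement and not a replacement. RRT practice and sample size are unchanged.

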### Procedure for unblinding if needed {17b}

Not applicable as no blinding was used in this trial.

## Data collection and management

### Plans for assessment and collection of outcomes {18a}

The assessment and collection of trial data will start at patient enrollment (D0) including vital signs, specific therapies (i.e., albumin, transfusions), vital organ support, blood, urine, and ascitic fluid tests, repeatedly up to D7.

The trial protocol includes the daily collection of an 8-h (480 min) urine volume, at blocked nocturnal interval from 23 to 07 h, for measurement of creatinine clearance, based on the following formula: creatinine clearance (mL/min) = (urinary creatinine [mg/mL] × urine volume [mL])/(serum creatinine [mg/mL] × urine collection time [480 min]) [34].

Daily blood analysis includes complete hemogram, coagulation, and biochemistry and arterial blood gas. Ascitic fluid will be collected with every new paracentesis and repeated every 48 h in the intervention group for screening of infectious complications.

Collected trial variables are mainly included in clinical severity scores APACHE II [35], SAPS II [36], CLIF-C ACLF [37], CLIF-SOFA, SOFA [38], RIFLE [30], KDIGO [29], ICA-AKI [13], MELD [39], and MELD-Na [40] and incorporate liver disease etiology, precipitant event for critical illness, urine output, serum creatinine, estimated and measured creatinine clearance, and number of days on RRT, Glasgow coma score and West-Haven scale, number of days under vasopressor support and dosage, PaO_2_/FiO_2_ ratio, positive end-expiratory pressure and number of days under mechanical ventilation, total bilirubin, coagulation international normalized ratio, platelet count, arterial blood lactate and prescribed albumin dosage. Intermediate effect variables IAP and APP will be measured throughout ICU stay to test the trial rationale.

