#### Control group—large-volume paracentesis

Ultrasound-guided (Ultrasound GE Vivid T8®) placement of an intra-abdominal catheter, 14 Gauge Optiva®, or similar, as indicated by the attending physician in accordance with international clinical guidelines [1, 12].Collection of ascitic fluid for laboratorial and microbiological analyses with every new paracentesis.Large-volume paracentesis will be performed as needed throught the ICU stay with a maximal duration of 8 h for each session.The volume of drained ascitis through LVP is determined by the attending physician, according to the usual clinical practice, without specified maximum volume limit.

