#### Intervention group—continuous passive paracentesis

Ultrasound-guided (Ultrasound GE Vivid T8®) placement of an intra-abdominal double lumen catheter, Kit Certofix® Duo720, or similar, for paracentesis.Aseptic Seldinger technique, with an acute angle of percutaneous needle insertion.Adhesive, suture-free, abdominal wall catheter fixation.Continuous passive ascitic fluid drainage, preferentially through the proximal lumen (lateral opening) to minimize obstruction.Collection of ascitic fluid every 48 h for laboratorial and microbiological analyses.The trial intervention catheter will be in place for a maximum duration of 7 days.The catheter should be removed after 7 days of intervention or prior to ICU discharge, whatever occurs first.After the 7th day of intervention, paracentesis should be performed using the standard LVP approach as needed.

The 7-day duration of the intervention was determined based on previous studies revealing that the cumulative prevalence of IAH reaches a relative steady-state 5 days after ICU admission, with a median ICU stay of between 5 and 8 days in the studied populations [17, 18]. Furthermore, the impact of IAH on renal disfunction, assessed by the rise in serum creatinine, may lag up to approximately 3 days [19]. Therefore, we considered reasonable a period of 7 day for the trial intervention, while minimizing the risk of paracentesis catheter-associated infection, albeit considered safe [20–22].

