#### Safety procedures and assessment

Clinical management will comply with current guidelines, including strict prevention, detection, and treatment of paracentesis-related complications, including paracentesis associated circulatory dysfunction, hypovolemia, intra-abdominal organ perforation and bleeding, catheter-related abdominal wall infection, and secondary peritonitis and abdominal wall fistula or bleeding [12]. Paracentesis-related complications and harm will be actively screened and reported by clinicians.

Paracentesis associated circulatory dysfunction is prevented with standard-of-care intravenous 20% albumin infusion (8 g for each 1 l of drained ascitic fluid) administered to all patients and, additionally, crystalloid infusion may be indicated by the attending physician to strictly avoid hypovolemia [12].

Intra-abdominal organ perforation and bleeding are prevented with (a) ultrasound guided paracentesis and (b) coagulopathy treatment, mandatory in case of severe thrombocytopenia (platelet count < 50,000/mL) or hypofibrinogenemia (< 0.7 g/L), as clinically indicated by the attending physician or the Blood Transfusion department [23–27].

Catheter-related abdominal wall infection and secondary peritonitis are to be prevented with aseptic paracentesis technique and standard catheter point of insertion surveillance for signs of inflammation or infection, similar to central venous catheter procedures [28].

We do not use prophylactic antibiotics along with the indwelling abdominal paracentesis catheter (IAPC) in the CPP intervention group nor in the control group.

The definition of secondary peritonitis includes the following: (1) polymorphonuclear cell count elevation > 50% in 48 h after the initial paracentesis or (2) microbiologic “de novo” isolation of bacteria after 48 h after paracentesis.

In case of isolated bacterial culture of suspected skin contaminants, without signs of infection, a new direct ascitic tap at a different site should be performed to confirm or exclude a diagnosis of secondary peritonitis.

Whenever a clinical diagnosis of secondary peritonitis is considered, then antibiotic treatment should be immediately started according to standard clinical practice.

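### Secondary peritonitis can be met only on repeat ascitic samples, which are scheduled in the continuous-drainage arm alone, so the crude infection comparison mixes a catheter effect with a testing effect

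*Protocol article*

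**What the plan says.** The protocol article, under Safety procedures and assessment, gives two alternative criteria for secondary peritonitis: "polymorphonuclear cell count elevation > 50% in 48 h after the initial paracentesis", or de novo "isolation of bacteria after 48 h after paracentesis".

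The sampling rules differ by arm:

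- **CPP:** "Collection of ascitic fluid every 48 h for laboratorial and microbiological analyses". The catheter stays in for up to 7 days and comes out at ICU discharge if that is sooner. Section {18a} says that sampling is "repeated every 48 h in the intervention group for screening of infectious complications".
- **LVP:** "Collection of ascitic fluid for laboratorial and microbiological analyses with every new paracentesis". There is no time schedule, because "paracentesis will be performed as needed".

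For the analysis, section {20a} states: "The absolute risk of paracentesis-related complications will be reported for both trial groups". Section {21b} plans a safety and outcome look after 30 patients, with termination for significant harm. Section {17a} leaves outcome assessment unblinded. The Discussion acknowledges that CPP may carry more infection than LVP.

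**The concern.** A patient can be counted as having secondary peritonitis only if fluid is examined again. In the CPP arm a second and later examination is built into the plan. In the LVP arm it happens only when a further tap is needed. A control patient with a single tap cannot meet either criterion, even if infected.

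Two effects follow, and both tend to count against CPP:

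- **Missed control cases.** Silent infections are found by screening in CPP and may go unseen in controls.
- **More chances of a false positive.** Each extra sample is another opportunity for a positive culture or a chance rise in cell count. The cell-count criterion is relative, with no absolute floor, so a small change from a low count qualifies.

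Infection is the main safety question about an indwelling catheter. If the crude risks differ, the reader cannot tell how much is the catheter and how much is the testing. The article gives no sign that the unequal sampling will be taken into account when the risks are set side by side.

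**Working it through.** The article gives no infection rate, false-positive rate or re-tap frequency, so there is no stated figure to reproduce. What follows is an illustration on labelled assumptions.

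**Inputs from the article.** 70 patients at 1:1, so 35 per arm; interim look at 30, so about 15 per arm; CPP sampling every 48 h for at most 7 days (168 h); cited median ICU stays of 5 to 8 days.

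**Scheduled repeat samples in CPP.** A full 168 h allows looks at 48, 96 and 144 h, so k = 3. A catheter removed at 5 days (120 h) allows looks at 48 and 96 h, so k = 2.

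**False positives.** Assume a chance f per sample of meeting the definition without infection, independent between samples. The risk over k repeats is 1 − (1 − f)^k.

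| f (assumed) | CPP, k = 2 | CPP, k = 3 | LVP, no re-tap | LVP, one re-tap |
|---|---|---|---|---|
| 2% | 4.0% | 5.9% | 0% | 2% |
| 5% | 9.8% | 14.3% | 0% | 5% |
| 10% | 19.0% | 27.1% | 0% | 10% |

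At f = 5% and 35 per arm, CPP would show 35 × 0.0975 = 3.4 to 35 × 0.1426 = 5.0 false cases, against 0 to 35 × 0.05 = 1.75 in LVP. With three CPP looks the gap is 14.3, 9.3, 4.5 and 0 percentage points for zero, one, two and three control re-taps.

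**Missed cases.** With the same true risk in both arms, the observed LVP risk is the true risk times the share of LVP patients re-sampled. A true risk of 10% with half re-sampled shows as 10% against 5%. A true risk of 20% with a quarter re-sampled shows as 20% against 5%. All these inputs are assumed.

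**Chance of a formally significant excess in CPP with no true difference.** Exact binomial enumeration, Fisher's exact test, two-sided p < 0.05, false positives only, f = 5%:

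| CPP looks v LVP re-taps | 15 per arm | 35 per arm |
|---|---|---|
| 2 v 1 | 0.5% | 2.7% |
| 2 v 0 | 1.2% | 12% |
| 3 v 1 | 2.5% | 11% |
| 3 v 0 | 5.1% | 38% |

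At f = 10%, the top of the assumed range, 3 v 1 gives 11% and 35%. Missed cases alone (true risk 5% to 20%, with 25% to 75% of LVP patients re-sampled) give 0% to 8% at 15 per arm and 0.2% to 33% at 35 per arm. With equal ascertainment the chance is at most 0.9% and 1.3%.

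**The case against.** Several objections have force.

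- **Controls are not unsampled.** Fluid is analysed at every new tap. Patients have at least grade 2 ascites, pressure is measured every 6 to 8 h, and therapy is titrated to keep it below 16 mmHg. Repeat taps are plausible, and if most controls were tapped at least every 48 h the bias would shrink or vanish. This stands, but the frequency is not stated and those taps follow need rather than a screening clock.
- **The look count is generous.** Read literally, the cell-count criterion covers only the 48 h after the initial tap. Later CPP samples could then qualify only on culture, and suspected skin contaminants without signs of infection require a confirmatory tap at another site. Catheters are also removed at ICU discharge, and looks within a patient are unlikely to be independent. This stands, and it makes the figures in the first table upper-end values.
- **The comparison is descriptive.** Complications are neither a primary nor a secondary outcome, and the Discussion admits low power for them. This stands, but descriptive risks shown by arm will still be compared.

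A reader might infer that the artefact would be expected to stop the trial for harm. The document does not support that. At 15 per arm and f = 5%, false positives alone give a significant excess in only about 0.5% to 5% of trials, and an independent three-member committee that includes a statistician reviews harm.

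A reader might also infer that screen-detected CPP infections should be left out of the comparison. That goes too far: some will be real, finding them is the stated purpose of the screening, and clinical suspicion in an open-label trial carries its own bias.

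**Conclusion.** The unequal ascertainment is real and follows directly from the text: the definition needs a later sample, only one arm has later samples scheduled, and risks are then reported by arm. The crude infection difference, in the final report and at the interim safety look, cannot be read as a catheter effect alone.

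The direction tends to be against CPP. The size is uncertain. On an assumed 5% false-positive rate per sample, about 10% to 14% in CPP against 0% to 5% in controls is the upper end, and the gap falls towards zero as control taps approach the CPP schedule. It does not follow that an observed excess would be spurious: a true catheter effect is possible, as the protocol itself says, and the present reporting could not separate the two. A false harm stop is possible but unlikely at the central assumption. The point deserves correction because it bears on the main safety question and the repair is cheap.

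**What to change.** Leave ascitic sampling and clinical care unchanged. Then:

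1. Record the reason for every ascitic sample in both arms: scheduled screen, new therapeutic tap, or clinical suspicion.
2. Keep all infections in the safety listing and the interim harm review, and show them there split by how they were detected.
3. Add a between-arm comparison limited to infections that were clinically prompted or clinically treated, under one rule for both arms. State beside it that open-label suspicion can still bias this comparison.
4. Report the number of ascitic samples and the patient-days per arm with every infection rate.

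The cost is one extra field on the case report form and one extra table. No event is hidden and no patient is managed differently.
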